#### Procedures

All mother/child pairs are assessed on three occasions: at baseline, 4 weeks following the intervention, and 6 months post intervention. For the baseline assessment, mothers are contacted by study recruiters and the study is explained to them. It is emphasised that participation is entirely voluntary and that non-participation carries no consequences. A suitable time for them to come to the Research Centre for assessment by the data collector is arranged. On arrival at the assessment session, consent is explained again and caregivers provide written consent for both themselves and their child. Assessments take 2 h and 20 min, on average. They comprise specific assessments of the child (e.g. language assessment), questionnaires completed by the caregiver (e.g. child behaviour), and filming the caregiver and child in interactive tasks (e.g. during book-sharing). There are breaks for refreshment and, if the child shows signs of tiredness or distress, the session is interrupted or, if necessary, terminated. Participants are given a small gratuity for contributing their time to the study. Similar procedures are followed for the subsequent two assessment waves. To prevent assessor bias, assessments of children and caregivers are being carried out blind to group allocation, with the at random allocation being conducted separately at the end of the baseline assessment. Participants are explicitly asked to not reveal their allocation to the data collectors in follow-up assessments. All coding of video material will be made blind to allocation.

#### Retention

Provisions have been put in place to maximise participant retention. This includes texts and phone calls to remind participants of scheduled assessments and sessions, fridge magnets to remind participants of the scheduled time, snacks, travel funds, and small gifts as well as a raffle for each study arm with the prize of a tablet. To increase adherence in the interventions, the mothers are: (1) shown videos about the benefits of the interventions, spoken by local mothers who had previously completed them, (2) taken by van to attend the first session and other sessions where their home is far from the intervention centre, (3) given travel funds for attendance at each session, (4) given snacks and a small gift for the children, and (5) provided with childcare during the sessions.

## Outcomes

### Assessments

Detailed assessments of the trial participants are being made at baseline and will be conducted on two occasions post intervention: 4 weeks following the end of the interventions and then at a the 6-month follow-up (see Table 3 below).

**Table 3 Tab3:** Study outcomes and measures

Outcome	Concept	Measures	Baseline (months 1–3)	Post intervention (months 4–6)	Follow-up (months 9–13)
Child aggression (primary outcome)	Child aggression	Aggression sub-scale of the Child Behaviour Checklist	✓		✓
		Items on aggression from the ELDEQ Study Questionnaire	✓		✓
		Observation: Don’t touch’ and ‘Clean Up’ tasks	✓		✓
		Observation: LabTab, ‘Don’t touch’ and ‘Clean Up’ tasks	✓		✓
Child language (main secondary outcome)	Expressive language	Teste de Vocabulário Expressivo	✓		✓
	Receptive language	Teste de Vocabulário Receptivo	✓		✓
Parenting (main secondary outcome)	Harsh and abusive parenting	PAFAS Questionnaire	✓		✓
		Juvenile Victimisation Questionnaire	✓		✓
		Observation: Don’t touch’ and ‘Clean Up’ tasks	✓		✓
		Searches of child protection service records			✓
Parenting (secondary outcomes)	Positive parenting	PAFAS Questionnaire	✓	✓	
		Videotaped sensitivity and reciprocity during book-sharing and free-play parent-child interactions	✓	✓	
	Parental attitudes about corporal punishment	Deater-Deckard study Questionnaire	✓	✓	
Stress (secondary outcomes)	Parental stress	Perceived Stress Scale	✓	✓	
		Pelotas questions on parenting stress	✓	✓	
	Parental and child chronic stress	Cortisol from hair samples	✓		✓
Child development (secondary outcomes)	Child attention	Strengths and Difficulties Questionnaire	✓		✓
		Card Sort task from the Early Years Toolbox			✓
	Child executive functions/self-control	Go no Go task from the Early Years Toolbox	✓		✓
		Block Design task	✓		✓
	Child emotion recognition	Denham’s puppet task	✓		✓
	Child empathy/theory of mind/altruism	Em-Que Questionnaire	✓		✓
		Help task	✓		✓
		Dictator Game			✓
		Triangle task	✓		✓
		Sally-Anne task			✓

The primary outcome is child aggression at the 6-month follow-up assessment, measured by parental report, and direct observation. The parent report measures include two questionnaires: the Aggression sub-scale of the Child Behavior Checklist (CBCL) [55] and items on aggression from the ELDEQ Study Questionnaire [39]. Three observational measures are being used: child response to a frustration task (from the *Laboratory Temperament Assessment Battery* for preschool children, www.uta.edu/faculty/jgagne/labtab), and child behaviour during ‘Don’t touch’ and ‘Clean Up’ tasks [56, 57]. The multiple measures of aggression will be combined into at least one latent variable for analysis of the primary outcome, and the independent trial statistician will decide if a single variable or multiple latent variables are required (for example, one for observed aggression and one for reported aggression).

The two main secondary outcomes will be measured at the 6-month follow-up. All relevant measures are being administered to the whole trial sample, but effects are hypothesised to be specific to DBS or ACT, as outlined above:Child language will be assessed using the Test of Receptive and Expressive Vocabulary (Teste de Vocabulário Auditivo e Teste de Vocabulário Expressivo http://memnon.com.br/produto/teste-de-vocabulario-auditivo-e-teste-de-vocabulario-expressivo/)Harsh and abusive parenting will be assessed by parent self-report, using the PAFAS Questionnaire [58], the Juvenile Victimisation Questionnaire (http://www.unh.edu/ccrc/jvq/index_new.html), by direct observation during the ‘Don’t touch’ and ‘Clean Up’ tasks [56, 57], and by searches of child protection service records

Additional secondary outcomes will be measured at the 4-week post-intervention assessment (#1–4 below) and at the 6-month follow-up (#5–8).Positive parenting will be assessed using the PAFAS Questionnaire, and videotaped sensitivity and reciprocity during book-sharing and free-play parent-child interactions (as successfully used in previous book-sharing trials) [31–33]Parental attitudes about corporal punishment will be assessed using by the Deater-Deckard Study Questionnaire [59]Parental stress will be assessed using the Perceived Stress Scale [60] and Pelotas questions on parenting stressParental and child chronic stress will be assessed by cortisol from hair samples [61–65]Child attention will be assessed using the Strengths and Difficulties Questionnaire [66] and the Card Sort task from the Early Years Toolbox [67]Child executive functions/self-control will be assessed using the Go no Go task from the Early Years Toolbox [67], the Block Design task, and assessor ratingsChild emotion recognition will be assessed using Denham’s puppet task [68]Child empathy/theory of mind/altruism will be assessed using the Em-Que Parent Questionnaire measure [69], the Help task [70], the Dictator Game [71], and the Sally-Anne task [72]

All the outcome measures specified above are being taken at baseline, except the Dictator Game measure of altruism and the Card Sort Game, which were judged to be less amenable to repeat application over a short period of time, and the Sally-Anne task (for empathy, the Triangle task [73] is being used at baseline, but concerns about how well it is functioning require an additional measure for follow-up)

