### Hypotheses

The study has three hypotheses:Compared to children of families who receive no intervention (the Control group), the children in families receiving DBS will show less aggression at follow-up, and they will perform better on measures of language, executive function, attention, and empathy/emotion understanding, but the parents will not show less harsh and abusive parentingCompared to children of Control group families, the children of families receiving ACT will show less aggression at follow-up and their parents will show less harsh and abusive parenting and less favourable attitudes about corporal punishment, but the children will not perform better on measures of language, executive function, attention, and empathy/emotion understandingFor both the DBS and ACT groups, children and parents will show less stress at follow-up, and parents will show more positive parenting

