### Sample size

Sample size has been calculated based on a projected effect size for each intervention of mid-range, moderate magnitude (*d* = 0.45) for the primary outcome at 6-month follow-up, based on findings of well-conducted previous trials of parenting interventions for child behavioural disturbance [23, 41–43]. With alpha at 0.025 (due to two pair-wise comparisons (i.e. between DBS and Control, and between ACT and Control), and beta at 0.20, each of the three trial arms requires a minimum of 104 participants (allowing for 10% attrition to the 6-month follow-up). To allow for identification of potentially smaller effects at 6 months, and continued follow-up of the trial participants in later phases of development, a sample size of 369 is being recruited in total.

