## Data analysis

Data analysis will be completed by a designated statistician, [name] from the Oxford University Department of Primary Care Medicine, who will work independent from study investigators. Group baseline differences will be investigated including socio-demographic data, such as child sex, and household factors (e.g. income, relationship status), and study outcomes.

The primary and secondary outcomes will be analysed using linear mixed models, which can account for repeated assessments within individuals (for outcomes measured at multiple time-points). Intervention effects will be assessed at post intervention and follow-up and will be adjusted for child’s age, sex, and baseline scores (where applicable). Further socio-demographic factors may also be investigated as covariates. If the necessary assumptions of the models do not hold, suitable alternative models will be fitted. Intention-to-treat analysis will be used to examine intervention effects. Sensitivity analyses will examine if intervention effects maintain for measures that are not dependent on parent report, which may be biased because parents are not blind to the interventions.

The amount and pattern of missing data will be examined and will be addressed using multiple imputation where appropriate. Due to the multiplicity of comparisons, caution will be used in interpreting results of secondary outcome comparisons. No single *p* value will be interpreted in isolation and all findings will be considered together to obtain the full picture of the intervention effects on the different outcome measures.

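### Effects on the two main secondary outcomes are called specific to one programme, but the hypotheses compare each programme only with Control and name no DBS-ACT contrast to test this

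*Protocol article*

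**What the plan says.** Hypotheses 1 and 2 each pair a predicted benefit with a predicted lack of benefit. Hypothesis 1 begins "Compared to children of families who receive no intervention (the Control group" and predicts that DBS improves child cognitive and social measures but does not reduce harsh parenting. Hypothesis 2 uses the same comparator and predicts the reverse for ACT.

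Under Outcomes, Assessments, the two main secondary outcomes (child language and harsh parenting) are introduced with the statement "All relevant measures are being administered to the whole trial sample, but effects are hypothesised to be specific to DBS or ACT, as outlined above". The reference back is to the hypotheses.

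The only pairwise comparisons listed by name are in Sample size, where alpha is set "due to two pair-wise comparisons (i.e. between DBS and Control, and between ACT and Control". That sentence concerns the primary outcome.

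Data analysis plans linear mixed models for primary and secondary outcomes and states: "Intervention effects will be assessed at post intervention and follow-up and will be adjusted for child’s age, sex, and baseline scores (where applicable". It asks for caution with secondary comparisons and says that p values will be read together rather than singly. It names no DBS-ACT contrast and does not say how a prediction of no effect would be judged.

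**The concern.** To say that an effect on language is specific to DBS is to say that DBS and ACT differ on language. A comparison of DBS with Control and another of ACT with Control do not estimate that difference. If one is significant and the other is not, the two programmes may still have the same effect, with chance placing one estimate above the threshold and the other below it.

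The no-effect clauses have a related weakness. A non-significant comparison with Control is compatible with no effect and also with a modest effect that the trial could not detect. The less precise the data, the more often such a clause would appear to be borne out.

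At stake is the interpretation of what distinguishes the two programmes: that one works through child cognition and the other through parenting. The claim that either programme reduces child aggression does not depend on it.

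**Working it through.** **Inputs from the protocol**
- Sample size: "With alpha at 0.025 (due to two pair-wise comparisons (i.e. between DBS and Control, and between ACT and Control), and beta at 0.20"; d = 0.45 on the primary outcome; "each of the three trial arms requires a minimum of 104 participants (allowing for 10% attrition to the 6-month follow-up"; "a sample size of 369 is being recruited in total".
- Data analysis: adjustment for age, sex and baseline score.

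**Assumptions (not in the protocol)**
- Equal allocation: 369 / 3 = 123 per arm. With 10% attrition, 123 × 0.9 = 110.7, about 111 analysed per arm.
- Independent observations and SD = 1.
- Covariates explain a share R² of outcome variance, taken from 0 to 0.5.
- Secondary outcomes tested at two-sided 0.05; results at 0.025 are also given.

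**Step 1. The plan's own figure.** n per arm = 2 × ((z₀.₉₈₇₅ + z₀.₈₀) / d)² = 2 × ((2.241 + 0.842) / 0.45)² = 93.9, so 94. Allowing for 10% attrition, 94 × 1.1 = 103.4 (rounded up to 104) or 94 / 0.9 = 104.4 (rounded up to 105). The stated 104 is reproduced with a two-sided 0.025.

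**Step 2. Precision of one comparison with Control.** SE = √(2(1 − R²) / 111), which is 0.134 for R² = 0, 0.116 for 0.25 and 0.095 for 0.5. The unadjusted 95% half-width is 1.96 × 0.134 = 0.26 SD. An estimate of exactly zero would therefore still leave effects up to d = 0.26 open. A true d = 0.30 would be non-significant 39% of the time with R² = 0 and 12% with R² = 0.5.

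**Step 3. A false specific pattern.** Suppose both programmes have the same true effect d. Let m = d / SE and c = 1.96. The two comparisons share the control arm, so their test statistics have correlation 0.5. The chance that the arm predicted to work is significant and the other is not is

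P = Φ(m − c) − Φ₂(m − c, m − c; 0.5).

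Example with R² = 0 and d = 0.30: m = 0.30 / 0.134 = 2.24; Φ(m − c) = 0.608; both significant = 0.448; P = 0.160.

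| R² | d = 0.20 | d = 0.30 | d = 0.45 |
|---|---|---|---|
| 0 | 14.8% | 16.0% | 5.7% |
| 0.25 | 16.1% | 13.5% | 2.3% |
| 0.5 | 16.5% | 7.5% | 0.2% |

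The formula peaks at m = c, where it equals 1/2 − 1/3 = 16.7%. The range for d = 0.2 to 0.3 is therefore 8% to 17% per outcome. At 0.025 the same cells run from 10.5% to 16.7% for d = 0.2 to 0.3, and are at most 8.5% for d = 0.45.

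**Step 4. The direct test.** DBS minus ACT has the same SE. When the two effects are equal its mean is zero, so at two-sided 0.05 it errs in the hypothesised direction 2.5% of the time, whatever d is. Its unadjusted power is Φ(D / 0.134 − 1.96) for a true difference D: 92% for 0.45, 61% for 0.30 and 32% for 0.20.

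**The case against.** Five arguments count against the point.

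- **Only a condensed article is at hand.** A statistical analysis plan may name a DBS-ACT contrast, and a three-arm model yields it from the same fit. This stands as a limit: the point is not that the article omits detail. The hypotheses and the word 'specific' are stated here, and the comparisons stated beside them do not test that claim.
- **No decision rule is written.** A reader might infer that the plan counts a non-significant comparison with Control as confirmation. The documents do not say so. They state predictions and leave open how these would be judged.
- **The pairwise comparisons in Sample size serve the primary outcome.** Correct: they are not a closed list for secondary outcomes. The Control-only framing of the secondary claims comes from the hypotheses themselves.
- **Data analysis urges caution and reads p values together.** This weighs against a mechanical reading, but it supplies no test. Looking at two comparisons with Control together is still not an estimate of their difference.
- **Specificity is not the trial's stated main aim.** Correct: the aim is efficacy in reducing child aggression. Moreover, the full predicted pattern needs both outcomes to fall the right way. If the outcomes were independent, that would happen by chance in about 0.6% (0.075²) to 3% (0.167²) of trials under equal effects.

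**Conclusion.** The point holds as a mismatch between a stated claim and the stated comparisons. It is confined to secondary outcomes. The primary comparison and the sample size are sound in this respect, and the 104 per arm is reproduced.

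If both programmes have the same true effect of d = 0.2 to 0.3, the hypothesised specific pattern would appear by chance in 8% to 17% of trials per outcome, against 2.5% for a direct test. The problem shrinks for larger common effects, to about 6% or less at d = 0.45. These figures use the 0.05 level and rest on equal allocation, 10% attrition, independent observations and R² between 0 and 0.5. Correlation within intervention groups would reduce precision and is not modelled.

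A reader might quote 15% to 33%, the chance that exactly one programme is significant at 0.05 for d = 0.2 to 0.3. That figure counts both directions, and only the hypothesised direction would be taken as support for specificity.

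**What to change.** In Hypotheses and Data analysis:

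- Name DBS minus ACT, with its confidence interval, from the mixed models already planned, as the test of specificity for child language and for harsh parenting.
- Reword the 'will not' clauses to say that no effect is predicted. Report the corresponding estimate against Control with its interval; the DBS-ACT contrast does not answer that question.
- State that a non-significant comparison with Control is not evidence of no effect.

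An equivalence margin is optional. With 111 per arm, no adjustment, a true effect of zero and two one-sided tests at 0.025, power would be 22% for a margin of 0.30 SD and nil for 0.225 or 0.20. These margins are illustrative; the protocol gives none.

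The cost is wording and two contrasts, with no new data. The price is that specificity will more often be reported as inconclusive, since the direct contrast has only about 61% unadjusted power for a difference of 0.30. Adjustment for baseline would improve this.

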### Potential moderators

The following variables will be examined as potential moderators: parental education, parental mental health, domestic violence, and maternal and child stress, maternal harsh parenting, number of siblings, and child sex, age, and aggression.

### Data management

Participants are being assured of the confidentiality and anonymity of their data. Data are being anonymised by using ID codes which are kept in secure storage on Federal University of Pelotas premises, with individuals’ personal, identifiable details kept separate from all other information. The anonymised electronic data will be archived at the Federal University of Pelotas, Centre for Epidemiological Research data storage and archive division (under the supervision of [name], Research Data Manager). Data will be made available to the academic community via requests being sent to the Pelotas Cohorts Publications’ Committee. Sensitive data will be stored in the archive under a restricted access setting, accessible to the data depositor and archive administrative staff only.

## Data analysis

Data analysis will be completed by a designated statistician, [name] from the Oxford University Department of Primary Care Medicine, who will work independent from study investigators. Group baseline differences will be investigated including socio-demographic data, such as child sex, and household factors (e.g. income, relationship status), and study outcomes.

The primary and secondary outcomes will be analysed using linear mixed models, which can account for repeated assessments within individuals (for outcomes measured at multiple time-points). Intervention effects will be assessed at post intervention and follow-up and will be adjusted for child’s age, sex, and baseline scores (where applicable). Further socio-demographic factors may also be investigated as covariates. If the necessary assumptions of the models do not hold, suitable alternative models will be fitted. Intention-to-treat analysis will be used to examine intervention effects. Sensitivity analyses will examine if intervention effects maintain for measures that are not dependent on parent report, which may be biased because parents are not blind to the interventions.

The amount and pattern of missing data will be examined and will be addressed using multiple imputation where appropriate. Due to the multiplicity of comparisons, caution will be used in interpreting results of secondary outcome comparisons. No single *p* value will be interpreted in isolation and all findings will be considered together to obtain the full picture of the intervention effects on the different outcome measures.

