**Methods:**

We are conducting a randomised controlled trial to evaluate two early parenting interventions for mothers of children aged between 30 and 42 months in a Brazilian city. The first of these, dialogic book-sharing (DBS), aims to promote child cognitive and socio-emotional development; and the second, the ACT Raising Safe Kids Program (ACT), is designed to reduce harsh parenting. These interventions are being compared with a control group receiving neither intervention. Three hundred and sixty-nine families in a birth cohort are being randomly allocated to one of the three groups (DBS, ACT, Control). Facilitators deliver the interventions to groups of five to 10 mothers at weekly sessions for 8 weeks in DBS and 9 weeks in ACT. Independent assessments of parenting and child development are being made before the interventions, shortly afterwards, and at follow-up 6 months later. The primary outcome is child aggression, and the two main secondary outcomes are: (1) child cognitive and socio-emotional development and (2) harsh parenting. Longer-term outcomes will be investigated as the birth cohort is followed into late childhood, adolescence, and adulthood.

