### Training and supervision of interventions

The Pelotas City Government is implementing the two interventions under the supervision of the research team. There are 11 DBS facilitators and 14 ACT facilitators working on The PIÁ Trial. Community workers from the State Primary Care for Children Programme in Pelotas (Primeira Infância Melhor) are delivering the DBS intervention (DBS). Education coordinators and social workers are delivering the ACT intervention.

Training in DBS has been provided to these community workers by [name] of the Mikhulu Trust (www.mikhulutrust.org) over a 5-day course, supported by TBS and MGA who were trained by PJC and LM. Training in ACT was provided through an in-person training workshop given by EA, a postdoctoral psychologist and ACT master trainer certified by the Violence Prevention Office of the APA. The ACT facilitators received further supervision and feedback by the ACT master trainer by distance (through video-taped sessions, a Google class room, and Skype discussions) and in-person by SC, a postdoctoral psychologist with clinical and child development experience. Both sets of training were conducted early in 2018, which allowed the intervention facilitators some months to practise the intervention techniques before their implementation in July 2018. During the implementation phase, TBS and MGA provide weekly supervision to the DBS facilitators and SC provides weekly supervision to the ACT facilitators with support from EA. A member of the research team is observing a random sample of 10% of group sessions and rating them for content to determine fidelity.

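### DBS and ACT are delivered in groups of mothers, but the 104 per arm allows for no clustering and the described mixed model names only within-individual correlation

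*Protocol article*

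**What the plan says.** The abstract of the protocol article gives the mode of delivery: "Facilitators deliver the interventions to groups of five to 10 mothers at weekly sessions for 8 weeks in DBS and 9 weeks in ACT". Under Training and supervision of interventions it adds: "There are 11 DBS facilitators and 14 ACT facilitators working". Under Study design the control arm receives nothing from the research team beyond the usual community services. Under Recruitment and randomisation, individual mother-child pairs are allocated by minimisation.

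Sample size assumes an effect of "mid-range, moderate magnitude (*d* = 0.45) for the primary outcome at 6-month follow-up". The error rates are "With alpha at 0.025 (due to two pair-wise comparisons" and "beta at 0.20, each of the three trial arms requires a minimum of 104 participants", with 10% attrition allowed for. Recruitment is then raised to 369 in total. Two reasons are given: "To allow for identification of potentially smaller effects at 6 months" and continued follow-up in later development. Clustering is not among them, and no ICC or design effect appears.

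Data analysis specifies "linear mixed models, which can account for repeated assessments within individuals (for outcomes measured at multiple time-points". Adjustment is for child age, sex and baseline score, possibly with further socio-demographic factors. No term for delivery group, facilitator or area is named.

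**The concern.** Mothers who spend eight or nine weeks in the same small group may come to have correlated outcomes. Controls have no such grouping. This is a partially nested design: randomisation is individual, and delivery creates clusters after randomisation in two of the three arms.

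The Data analysis section does speak about correlation, but the correlation it names is a different one. In Table 3 each measure is ticked at either the post-intervention visit or the 6-month follow-up, never both. With baseline entered as a covariate, each outcome contributes one value per child, so a within-individual random effect has almost nothing to estimate. The dependence that the design does create is not named.

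Two things are at stake. A model without a group term gives confidence intervals that are too narrow and false-positive rates above 0.025 in both primary comparisons, which undercuts the split of alpha. In addition, the stated power basis is more favourable than the design supports.

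**Working it through.** **Inputs from the article.** d = 0.45 (SD 1), alpha 0.025 per comparison, power 80%, attrition 10%, minimum 104 per arm, 369 recruited, group size m = 5 to 10, controls ungrouped.

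**Assumptions.** Two-sided tests and 1:1:1 allocation (369/3 = 123 per arm). The article gives no ICC, so 0.02, 0.05 and 0.10 are used.

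**Step 1: reproduce 104.** n = 2(2.2414 + 0.8416)²/0.45² = 93.9 per arm, and 93.9/0.9 = 104.3. This matches the stated 104 and leaves no room for a design effect. A one-sided 0.025 gives 78 (87 with attrition) and does not reproduce it.

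**Step 2: partially nested variance.** Only the active arm is inflated, with DE = 1 + (m − 1)·ICC. The variance of the difference is (DE + 1)/n instead of 2/n. Analysed n is 104 × 0.9 = 93.6 or 123 × 0.9 = 110.7.

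- Power = Φ(0.45/√((DE + 1)/n) − 2.2414)
- True type I error if group is ignored = 2[1 − Φ(2.2414·√(2/(1 + DE)))]
- Detectable effect at 80% power = (2.2414 + 0.8416)·√((DE + 1)/110.7)

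| ICC | m | DE | True type I error (nominal 0.025) | Power, 104/arm | Power, 123/arm | Detectable d, 123/arm |
|---|---|---|---|---|---|---|
| 0 | – | 1 | 0.025 | 79.9% | 86.6% | 0.414 |
| 0.02 | 5 | 1.08 | 0.028 | 78.2% | 85.1% | 0.423 |
| 0.02 | 10 | 1.18 | 0.032 | 76.0% | 83.3% | 0.433 |
| 0.05 | 5 | 1.20 | 0.033 | 75.6% | 82.9% | 0.435 |
| 0.05 | 7.5 | 1.325 | 0.038 | 73.0% | 80.6% | 0.447 |
| 0.05 | 10 | 1.45 | 0.043 | 70.5% | 78.3% | 0.459 |
| 0.10 | 5 | 1.40 | 0.041 | 71.5% | 79.2% | 0.454 |
| 0.10 | 7.5 | 1.65 | 0.052 | 66.7% | 74.8% | 0.477 |
| 0.10 | 10 | 1.90 | 0.063 | 62.4% | 70.5% | 0.499 |

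**Step 3: break-even at 123 per arm.** Power is 80% when DE + 1 = 110.7 × (0.45/3.083)² = 2.358. So ICC = 0.358/(m − 1), which is about 0.090 for m = 5, 0.055 for m = 7.5 and 0.040 for m = 10.

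**Limits.** The calculation uses a normal approximation. It ignores unequal group sizes, non-attendance and the small number of clusters (123/10 to 123/5, about 12 to 25 per active arm). It also ignores the gain from baseline adjustment, as does the article's own calculation.

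**The case against.** The Data analysis section describes a class of model and does not list every random effect. It does not exclude a delivery-group term, it allows alternative models if assumptions fail, and it gives the work to an independent statistician. A journal article commonly leaves the random-effects structure to an analysis plan, which is not shown. This stands as a limit on certainty: the inflated error rate is conditional on fitting the model as described. It does not dispose of the point, because the section states which correlation the model is for and names one that Table 3 makes nearly irrelevant. An unseen plan also could not alter the basis of the 104 in Sample size.

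A reader might infer that the trial lacks 80% power. The documents do not support that. The 80% belongs to the minimum of 104, while 123 per arm are being recruited, and that surplus absorbs an ICC of about 0.04–0.09 depending on group size. Baseline adjustment helps further. If one assumes a baseline correlation of 0.3–0.5 that reduces only the non-group variance, power at 123 per arm, ICC 0.05 and groups of 10 is about 82–87% instead of 78%. Groups of 10 may also be untypical: 369/3/11 = 11.2 mothers per arm per area exceeds the maximum group size, so two groups of about 5.6 are plausible. At ICC 0.05 that gives 82% power and a type I error of 0.034.

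A reader might also infer that the scope for finding smaller effects is gone. It shrinks, but the detectable effect stays below 0.45 throughout at ICC 0.02, and at ICC 0.05 for groups of 5 and 7.5.

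Finally, the article does not say that each group kept one facilitator, or that group membership is recorded. Neither is relied on here.

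One part is untouched by these replies. Neither the surplus recruitment nor baseline adjustment repairs a standard error that leaves group out.

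**Conclusion.** The point holds in a conditional form. It is established from the article that delivery is in groups in the two active arms only, that 104 per arm contains no clustering allowance, and that the one correlation named for the model is not the one the design creates.

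The consequence for the tests needs a positive group ICC and a final model without a group term. Under those conditions both primary comparisons are anti-conservative: about 0.033–0.043 at ICC 0.05 and 0.041–0.063 at ICC 0.10, against 0.025. The consequence for power is certain only at the minimum of 104 per arm, where any positive ICC brings it below 80%. At 123 per arm the loss is moderate and depends on an ICC that the documents do not give.

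**What to change.** In Data analysis, state that each outcome model includes a random intercept for delivery group in the DBS and ACT arms only, with each control mother as her own cluster. State also that a small-sample degrees-of-freedom correction is used and that non-attenders stay in the group to which they were assigned. Group membership should be obtainable from delivery records, and this should be confirmed.

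In Sample size, say that 104 per arm assumes no clustering, and give power and detectable effect at 123 per arm for ICCs from 0.02 to 0.10.

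Enrolment does not change. By Trial status, 304 of the 369 had been recruited when the manuscript was submitted. The change costs some wording and one variance term. The downside is slightly wider intervals and a less favourable stated power.
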